**Fig. 3 Fig3:**
[figure not shown]
Intervention procedures

In all cases, participants will immediately be provided with feedback on the accuracy of their choice, the correct answer, and a reinforcing message such as “HIV prevalence is higher amongst older men.”

Following insights from behavioral economics, the study will also implement a non-binding commitment device to enhance participants’ engagement. In particular, all individuals will be encouraged to provide their contact numbers and a preferred time for contact by a nurse from the health clinic to discuss PrEP further and make an appointment for a visit.

Participants will also be provided with a PrEP referral letter that they can present directly at one of the participating study clinics to begin PrEP. This article adhered to the Standard Protocol Items: Recommendations for Interventional Trials (SPIRIT) 2013 checklist (see Additional file 1 and  Fig. 4).

**Fig. 4 Fig4:**
[figure not shown]
Timeline of study procedures

#### Further procedures for clusters with community-led interventions

A participatory reflection and action (PRA) approach to community engagement will be used. The approach of involving local community structures in addressing health challenges is based on strong theoretical foundations [17, 18] and has been applied successfully in other health programs [19–21] and to tackle gender-based violence in the context of HIV [22]. This approach supports critical thinking and problem solving around key community issues through CCs. CCs involve posing questions and thinking points to formal community groups or informal networks around community challenges and about potential local responses and community resources to tackle these. In Zimbabwe, CCs have helped to raise community HIV competence [23]. This study will be the first to explore whether and how CCs—as a community engagement strategy—can break down community-level barriers with implications for uptake of PrEP. In these clusters, the Diocese of Mutare Community Care Programme (DOMCCP) will initiate and support a process to: (1) mobilize and work with pre-existing village structures and local community groups who have demonstrated a commitment to fight HIV [24]; (2) conduct CCs with formal groups at village level, generating community action plans; and (3) provide modest funding and technical support to community groups to implement their planned activities. A toolkit on CCs for HIV prevention has been developed to assist the facilitators, standardizing the process and ensuring that CCs stay focused on HIV prevention strategies for AGYW and male partners. The toolkit has been designed to complement the PrEP intervention by: (1) instigating discussions on HIV risk – cementing the salience of HIV prevention methods and on social preferences and biases to use of PrEP; (2) identifying innovative community-led solutions that help AGYW and young men overcome social barriers and re-think risk perceptions; and (3) developing clear steps for communities to prevent the spread of HIV, drawing on local knowledge, resources, and existing local activities. Practically, each CC will comprise 10–15 people who, in four sessions, will: (1) share personal experiences; (2) discuss the challenges/factors preventing AGYW and partners from using HIV prevention methods; (3) explore how to respond; and (4) agree on steps to include in action plans and identify the necessary resources. The community groups will then implement, evaluate, and update their plans.

### Inclusion and exclusion criteria

A total of 1200 women will be considered eligible if: (1) they are aged 18–24 years; (2) they live in the intervention cluster (see below) in one of the eight study sites in Manicaland province; and (3) they expect to be resident there for the duration of the study. Participants will be excluded if they test positive for HIV at baseline or self-report taking PrEP at baseline. To avoid indirect disclosure of the status of HIV-positive individuals, a random sample of 90% of otherwise eligible HIV-negative women will be selected to participate in the intervention.

### Randomization/masking

In each study site, community leaders will first be contacted and clearance will be sought to carry out activities. In addition, community meetings will be organized to introduce the activities before the start of any procedures. Within each of the eight study sites (including the two sites with the additional CC intervention component), detailed site maps will be used to create two matched clusters of villages based on socioeconomic characteristics and factors such as distances to trading centers, major roads, and health centers. Clusters within a site will be randomly allocated to intervention or control using a simple coin toss process. Thus, all eight sites will contain two clusters each (intervention and control). Young women in intervention clusters will receive the interactive intervention (and in two sites, CCs will also be implemented). Young women in the control villages will receive no intervention and will be followed up for measurement of outcomes at six months. Participants will not be masked for the intervention they receive due to cluster level randomization and the nature of the intervention. Study interventions and measurements will occur in separate locations and time points thus facilitating the blinding of outcomes assessors.

### Primary and secondary outcomes

HIV prevention cascades (HPCs) have been proposed to facilitate identification of gaps in implementation of primary HIV prevention methods, understanding of the reasons for these gaps, and identification and evaluation of promising interventions to address the gaps [25, 26]. The population of HPCs using existing study data motivated the selection of some of the outcomes for this study. While no prior measurements were available to populate a HPC specifically for PrEP, analyses of the HPC for existing prevention methods among AGYW in the study population [25, 26] found major gaps in perceptions about personal risk of HIV infection.

The primary outcome for the study will be the proportion of women taking up PrEP within six months measured via biomarkers of ARV presence from DBS and triangulated with self-reports and clinic data. The secondary outcomes will be risk perception measured at baseline and in a follow-up survey at six months, and self-reported change in sexual behavior between baseline and follow-up surveys.

### Sample size estimates

It is estimated that a sample size of 600 participants per arm would be necessary to detect meaningful minimum effect sizes (around 20%) for the primary endpoint (PrEP uptake), with 80% power (*α* = 0.005). Survey data from the study sites in 2012–2013 were used to calculate mean cluster size, coefficient of variation in cluster size (0.15 for women), and the intra-cluster correlation coefficient (ICC) (0.04 using HIV incidence as the outcome). Baseline prevalence estimates of endpoint indicators were assumed to be 10% for PrEP. It was also assumed that 80% of eligible participants consent to participate and that 80% of these are followed up at six months (mean cluster size of 48). The exploratory nature of the intervention combining interactive counselling and community engagement means that we have chosen to use only two clusters for this intervention as this allows greater power to detect the effect without the community-level intervention. Nevertheless, in the two sites with the combined intervention, the study is powered to detect large impacts (effect size difference = 40%) on the outcome indicators. As a further consequence, there is not sufficient power to examine the interaction of the effect sizes with and without the addition of the community-level intervention.

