### Statistical analysis

Analysis of the primary outcomes will be done on an intention-to-treat basis. For each endpoint, a linear regression will be used to estimate differences in the cluster-level prevalence of the indicator at follow-up. The intervention and control clusters in the six study sites with only the digital interactive counselling will be compared in one analysis. A separate analysis will compare intervention and control clusters in the two study sites which also include the community conversations component. Any indicators unbalanced at baseline will be included as covariates. The Shapiro–Wilk normality test will be used to test for non-normality of the model residuals, and standard non-parametric tests (e.g. Mann–Whitney rank-sum test) will be used in case of non-normality. Effect sizes will be reported with 95% confidence intervals and results will be considered significant if *P* < 0.05. Data will be analyzed using STATA version 15.

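### The sample size section gives 80% power at α = 0.005 with 600 women per arm, but the planned tests use P < 0.05 on six and two site pairs, so the printed α and N fit no planned comparison

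*Protocol article*

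**What the plan says.** Under *Sample size estimates*, the protocol article states: "It is estimated that a sample size of 600 participants per arm would be necessary to detect meaningful minimum effect sizes (around 20"%), "with 80% power (*α* = 0.005"). The inputs given there are:

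- an ICC of 0.04, taken from HIV incidence;
- cluster sizes with a "coefficient of variation in cluster size (0.15 for women");
- 80% consent and then 80% follow-up, giving a mean cluster size of 48;
- "Baseline prevalence estimates of endpoint indicators were assumed to be 10% for PrEP".

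The same section says the two sites with community conversations are powered for an effect of 40%.

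Under *Statistical analysis*, each endpoint is analysed by linear regression on cluster-level prevalence. "The intervention and control clusters in the six study sites with only the digital interactive counselling will be compared in one analysis", and the two combined-intervention sites are analysed separately. The threshold is given as follows: "Effect sizes will be reported with 95% confidence intervals and results will be considered significant if *P* < 0.05".

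Under *Inclusion and exclusion criteria*, the total of 1200 refers to eligible women, and women who report taking PrEP at baseline are excluded.

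**The concern.** Three printed elements do not fit together.

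1. **Significance level.** The trial is sized at 0.005 and tested at 0.05, and the article does not link the two. A result at p = 0.02 would be significant under the analysis section but not at the level used for sizing.
2. **Sample size.** The 600 per arm covers eight sites before losses to consent and follow-up. No planned analysis pools eight sites, and no N is given for the six-site comparison.
3. **Method.** The planned test has 12 data points in the six-site comparison and 4 in the two-site comparison. With so few, a normal approximation and a t-based calculation differ widely, above all at α = 0.005.

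Two labels add to the difficulty. A 10% baseline prevalence of PrEP use cannot describe women from whom current users are excluded, so it can only serve as control-arm uptake at six months. And an effect of around 20% has no stated scale.

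At stake is how the result is read. The Discussion relies on the calculation as evidence of adequate power, and a null result would be judged against a detectable difference that belongs to a different α.

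**Working it through.** **Inputs** (*Sample size estimates* unless stated): control 10%; intervention 30%, reading 20% as percentage points; m = 48; ICC = 0.04; CV = 0.15; k = 6 and k = 2 clusters per arm (*Statistical analysis*). Sidedness is not stated; two-sided is assumed.

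**What the 600 is.** 600 × 0.8 × 0.8 = 384 = 8 × 48, the whole trial. Each cluster has 48 / 0.64 = 75 eligible women. Six pairs have 6 × 75 = 450 eligible and 6 × 48 = 288 followed up per arm. Two pairs have 150 and 96.

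**Design effect.** 1 + [(1 + 0.15²) × 48 − 1] × 0.04 = 2.92.

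**Standard error of the difference.** √{2.92 × [p₁(1−p₁) + p₂(1−p₂)] / (48k)}

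- k = 6, 10% vs 30%: √(2.92 × 0.30 / 288) = 0.0552; ratio 0.20 / 0.0552 = 3.62.
- k = 8, 10% vs 30%: √(2.92 × 0.30 / 384) = 0.0478; ratio 4.19.
- k = 2, 10% vs 50%: √(2.92 × 0.34 / 96) = 0.1017; ratio 3.93.

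**Reproducing the stated 80%.** For six pairs, the normal approximation at 0.005 gives Φ(3.62 − 2.81) = 79%, with a detectable difference of 20.2 points. For two pairs, the same approach gives a detectable difference of 37 points (unpooled variance) or 40 (pooled). These are close to the article's 20% and 40%. At 0.05 the normal formula gives about 15 points for six pairs and 28 to 29 for two, which match neither figure.

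Eight pairs come near 80% in a different way: a t-test with 14 df at 0.005 gives 78%. Likewise the formula needs 6.08 clusters per arm, and adding two for matching gives 8.08 × 75 = 606.

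**Power under the planned cluster-level regression** (noncentral t, 2k − 2 df, no covariates):

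| Comparison | Effect | α | Normal | t-based |
|---|---|---|---|---|
| Six pairs (10 df) | 10% vs 30% | 0.005 | 79% | 55% |
| Six pairs (10 df) | 10% vs 30% | 0.05 | 95% | 90% |
| Two pairs (2 df) | 10% vs 50% | 0.005 | 87% | 8% |
| Two pairs (2 df) | 10% vs 50% | 0.05 | 98% | 55% |

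For six pairs, the detectable difference at 80% power with 10 df is about 26 points at 0.005 and about 17 points at 0.05.

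**Scale of the effect.** If around 20% meant a rise from 10% to 20%, six pairs at 0.05 would have 43% power (10 df). For a relative rise, 10% to 12%, power would be about 6%. Neither reading reproduces 600 or 80%, so percentage points is the reading that fits.

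**The case against.** The strongest defence is that the authors did calculate on the split they analyse. Six and two pairs by the normal formula at 0.005 give roughly 20 and 40 points, and the section explains that the combined intervention was limited to two sites to keep power for counselling alone. This defence largely stands. A reader might infer that the 80% belongs to an eight-site comparison the trial will never make. The figures do not establish that, because the eight-pair route to 80% does not account for the 40%. What is left is that the 600 was quoted without the six-pair N, and that the normal approximation does not suit 12 observations.

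The second defence is that sizing at a stricter level than the test is conservative. For the six-site comparison it is: at 0.05, power for 20 points is 90%. It does not carry over to the two-site comparison, and the article does not offer it as a reason.

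Third, a condensed article may leave the method of calculation to a fuller document. That covers the choice between normal and t. It does not cover two different significance levels printed for the same endpoint.

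The ICC from HIV incidence is a disclosed proxy, in an article that says no earlier data were available to populate a PrEP cascade. It is not counted as an error here.

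**Conclusion.** The point holds as a misstatement. The printed α is not the test α, the printed N is a whole-trial eligible count, and the stated 80% is not the power of the planned regression at either level: it is about 55% at 0.005 and about 90% at 0.05 for six pairs and 20 points.

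A reader might infer that the six-site comparison is underpowered. The documents do not support that. At the threshold the analysis section sets, power exceeds 80% and the detectable difference is about 17 points. It would still be 82% if site terms were added (5 df, no gain credited to matching), though the article specifies no site terms. The 55% applies only if 0.005 is the true threshold.

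Nor should 0.005 be assumed to be a misprint, since the stated effects fit it better than 0.05. Only the sponsor can say which level was meant.

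The two-site claim is weaker. With four clusters and 2 df, a 40-point effect has about 55% power at 0.05 and 8% at 0.005.

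These figures assume a two-sided test, the stated ICC, percentage points, and 10% control uptake at six months. On an ICC range chosen for illustration, six-pair power at 0.05 (10 df) is 81%, 72% and 64% at 0.06, 0.08 and 0.10. The article does not call the six-site comparison primary; that it is the main one is inferred from the stated wish to preserve its power.

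**What to change.** - Use one two-sided α in both sections (0.05 if *Statistical analysis* governs), or state why the design and test levels differ. Settle this before outcome data are analysed.
- Give the counselling-only comparison its own line: six site pairs, 450 eligible and 288 followed up per arm, with t-based power for the cluster-level regression. At 0.05 this is about 90% for 10% vs 30%, with about 17 percentage points detectable at 80% power.
- Restate the two-site 40% claim on the same basis: four clusters, 2 df, about 55% power at 0.05 and about 8% at 0.005.
- Label the 600 per arm as eligible women over all eight sites.
- Express effects in percentage points, and describe the 10% as control-arm uptake at six months.

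The cost is revised wording and a short recalculated table. No extra participants are needed.

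### The two-site comparison with community engagement is called powered for a 40-point difference, but the planned analysis of two against two clusters has about 55% power.

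*Protocol article*

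**What the plan says.** Under Randomization/masking, each of the eight sites is split into two matched clusters, one per arm. Two sites add community conversations to the tablet session. Under Sample size estimates the authors call this combination exploratory and write "we have chosen to use only two clusters for this intervention", so as to protect power for the main comparison. They then state that in those two sites "the study is powered to detect large impacts (effect size difference = 40%) on the outcome indicators". The only shortage of power they concede is for the interaction between the two forms of intervention.

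Under Statistical analysis, each endpoint is compared by linear regression on cluster-level prevalence at follow-up. For the sites in question, "A separate analysis will compare intervention and control clusters in the two study sites which also include the community conversations component". Indicators unbalanced at baseline enter as covariates. Residuals are checked with the Shapiro–Wilk test, and "standard non-parametric tests (e.g. Mann–Whitney rank-sum test) will be used in case of non-normality". The threshold is stated as "results will be considered significant if *P* < 0.05", with 95% confidence intervals.

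**The concern.** A regression on four cluster values, with an intercept and an arm term, leaves 2 residual degrees of freedom. The critical t is then 4.30, against 1.96 for a normal reference. A site term or one covariate leaves 1 degree of freedom and a critical value of 12.71. A power statement that does not allow for this can be far too optimistic.

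This comparison is the trial's only randomised evidence on the combined intervention, and the article describes the study as the first to explore whether community conversations affect PrEP uptake. A reader told that it is adequately powered may take a non-significant result as evidence of no large effect, when the data could not support that.

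The fallback adds a second problem: a rank-sum test on two against two values cannot reach the stated threshold whatever the data.

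**Working it through.** **Inputs, all from the article.** Two clusters per arm in this comparison; control uptake 10%; mean analysed cluster size 48 (600 × 0.80 × 0.80 / 8 = 48); ICC 0.04; CV of cluster size 0.15; α = 0.005 under Sample size estimates and 0.05 under Statistical analysis.

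**Assumptions.** The 40% is in percentage points (10% against 50%), tests are two-sided, and the regression has no site term, since none is specified. No power is printed beside the 40% sentence; 80% is carried over from the main calculation.

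**1. Design effect.** 1 + ((0.15² + 1) × 48 − 1) × 0.04 = 2.923.

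**2. Reproducing the claim with a normal reference.** Effective size per arm is 2 × 48 / 2.923 = 32.84.
- Pooled formula at α = 0.005: z = (0.40 × √32.84 − 2.807 × √(2 × 0.30 × 0.70)) / √0.34 = (2.292 − 1.819) / 0.583 = 0.81, so power is 79% (80% if the CV is ignored).
- Unpooled formula: 87% at α = 0.005 and 98% at α = 0.05.

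The main comparison behaves similarly. With six clusters per arm, 10% against 30% and α = 0.005, the unpooled z gives √(0.30 × 2.923 / 288) = 0.0552, then 0.20 / 0.0552 − 2.807 = 0.82, or 79%. The 40% statement therefore fits a normal approximation.

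**3. Power of the analysis as written.**
- SE of the difference: √((0.10 × 0.90 + 0.50 × 0.50) × 2.923 / 96) = 0.1017.
- Noncentrality: 0.40 / 0.1017 = 3.93.

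| Analysis of 2 v 2 clusters | df | α | Critical t | Power |
|---|---|---|---|---|
| As written | 2 | 0.05 | 4.30 | 55% |
| With a site term or one covariate | 1 | 0.05 | 12.71 | 24% |
| As written, at the sample-size α | 2 | 0.005 | 14.09 | 8% |

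Beta-binomial simulation of the first row gives 57%. The 95% CI half-width is 4.303 × 0.1017 = 0.438, about 44 points and so wider than the 40-point target. The difference detectable with 80% power is about 55 points.

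**4. Sensitivity to the ICC.** The 0.04 comes from HIV incidence, not PrEP uptake. At 2 df and 48 per cluster, power is 79% at ICC 0.01, 69% at 0.02, 46% at 0.06 and 35% at 0.10. The ICC must be about 0.009 or lower to reach 80%.

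**5. Rank-sum fallback.** Four values can be split two and two in C(4,2) = 6 ways, so the smallest two-sided exact P is 2/6 = 0.333. The normal approximation gives z = 2 / √(5/3) = 1.55 and P = 0.12. Neither can fall below 0.05.

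In the unpaired model the four residuals are ±a and ±b, and Shapiro–Wilk rejects when a and b are nearly equal. With every cluster at 48 women it rejects in about 7.5% of simulated trials, and power for the whole procedure falls from 57% to 51%. Exact ties in size inflate that rate: when I let cluster sizes vary with CV 0.15, it rejected in about 4% and overall power was about 55%.

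**6. Joint model as an alternative.** One regression over all 16 clusters, with site indicators, arm, and arm by community-engagement site, has 6 residual df. Power is about 90% and the half-width about 25 points, if residual variance is common to all sites. I simulated no intervention effect with unequal base uptake (scenarios assumed, not from the article). The nominal 5% test of the two-site effect then rejects in about 14% (30% uptake in these sites, 10% elsewhere) or 16% (50% and 10%). With 20% and 5% it rejects in about 19%.

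**The case against.** The best defence is that the sentence is not a slip of arithmetic: it reproduces at 79–80% from the article's own inputs. That stands. The fault is the reference distribution, which does not match the analysis specified.

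The trial is also a pilot, the combination is called exploratory, and the six-site comparison is separate and unaffected. This limits the consequence. It does not withdraw the claim, because the article uses the exploratory label to explain the choice of two clusters and then asserts power all the same.

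Other readings of the inputs do not rescue it. One-sided testing at 0.05 would give 79%, but it is not stated and does not fit 95% intervals. A relative 40% (10% against 14%) would give about 6%.

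Three stronger conclusions are tempting but not supported:
- **Most true 40-point effects would be missed.** At 55%, slightly more than half would be significant. Missing most requires 1 df or α = 0.005, and the analysis section specifies no site term and sets 0.05.
- **The fallback dooms the comparison.** It is fatal only when triggered, which is uncommon in the unpaired model. The rank-sum test is also named only as an example.
- **The joint model should replace the separate analysis.** It borrows variance across towns, estates, villages and urban suburbs, and its type I error can be well above 5%. The separate analysis avoids this.

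**Conclusion.** The power statement is wrong for the analysis the article specifies. Power for a 40-point difference is about 55%, not the implied 80%, and about 24% if a site term or one covariate is added. Nearly half of true 40-point effects would be non-significant. The fallback cannot yield significance when triggered, which costs up to about 6 further points of power.

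These figures rest on two-sided testing, a percentage-point reading of the 40%, the article's ICC and cluster size, and an unpaired regression. The finding is confined to the secondary two-site comparison and does not touch the six-site result.

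**What to change.** - **Sample size estimates.** Delete the claim of power for a 40% difference, or restate it: about 55% power for 40 points, or about 55 points detectable with 80% power. State the α that applies, since the two sections differ.
- **Statistical analysis.** Label the two-site comparison descriptive and report the estimated difference with a t-based 95% confidence interval. Drop the rank-sum fallback for this comparison.
- **Optional.** Add the 16-cluster joint model as a sensitivity analysis only, stating its assumption of common residual variance and the risk of inflated type I error.

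This costs a few sentences in two sections. No change to design, recruitment or data collection is needed. What is given up is a claim of confirmatory power that the two sites cannot deliver.
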